## Interventions

### Preparation Before the Block

All participants will be placed in the lithotomy position with a multi-parameter monitor. The participant's blood pressure, heart rate and breathing rate will be measured automatically every min, from 1 min before the anaesthesia procedure to 1 min after the prostate biopsy process. A urologist will be informed of which block method to perform on the spot after the research nurse open a sealed envelope.

### Perineal Nerve Block Arm

The participants in this arm will undergo a perineal nerve block before a prostate biopsy. The insertion site on the skin will be located on the horizontal line of the anal canal at the upper margin, 20 mm beside the midline. First, the insertion site will be anaesthetized with 10 ml of 1% lidocaine with a 22-gauge 32 mm needle. Then, an advanced injection of perineal nerve block will be carried out with a 20-gauge and 80 mm needle. We will inject 5 ml of 1% lidocaine at each site of the perineal nerve bundle under the guidance of a biplanar ultrasound transducer (Figures 2, 3A).

**Figure 2 F2:**
[figure not shown]
Diagram of the location of the perineal nerve block: The 2 grey dots are the block sites.

**Figure 3 F3:**
[figure not shown]
The biplanar transrectal ultrasound image. **(A)** Perineal nerve block. **(B)** Periprostatic block: prostate (red arrow); pubis (yellow arrow); seminal vesicle (green arrow); anaesthesia needle (blue arrow); perineal nerve block site (orange dot); periprostatic site (purple dot).

### Periprostatic Block Arm

In this arm, the periprostatic block procedure will be performed *via* an 80 mm 20-gauge needle under the guidance of the ultrasound probe after the skin is anaesthetised by 10 ml of 1% lidocaine *via* a 22-gauge 32 mm needle. The block region will be located on the basal prostatic capsule, lateral to the location between the prostate and seminal vesicle (Figure 3B). Additionally, 5 ml of 1% lidocaine will be injected at each site.

### Prostate Biopsy

Another urologist who is blinded to the block method will perform the prostate biopsy. All patients will undergo a 12-core systematic transperineal prostate biopsy with or without a targeted biopsy. The 12-core systematic biopsy region will be taken as described previously (14). A targeted biopsy will be performed using the cognitive fusion method (15), only when there is at least one suspicious lesion [defined as a lesion with a score ≥3 according to the Prostate Imaging Reporting and Data System (PI-RADS) criteria (16)] shown by the MRI. Another research nurse who is also blinded to allocation will record the manifestations of the patients during the biopsy procedure.

### Histology

The pathologic results will be reported within 14 days after the biopsy according to the ISUP guidelines (17). The pathologists who assess the biopsy samples will be blinded to all clinical data including the anaesthesia technique. The Gleason score, the length of the tumour, and the percentage of the tumour will be reported for each needle sample. Clinically significant cancer cases will be defined as those with a ISUP score of 2 or higher.

### Sample Size

The prospective data in our previous study showed a mean maximal VAS score of 1.8 for patients who underwent a biopsy with a perineal nerve block and a mean maximal VAS score of 3.4 for those who received a periprostatic block. The standard eviations for these two methods were 1.02 and 0.96, respectively.

For the calculation of sample size, using a power of 90%, a two-sided α of 5%, and an allocation ratio of 1:1 and assuming an NRS score for the perineal nerve block of 2.0, an NRS score for the periprostatic block of 2.5, and the standard deviations for these two methods are equal to 1.0, 86 men per arm will be required. Accounting for a withdrawal/loss rate of 10%, a total of 190 participants are required for inclusion.

### Statistical Analysis

The primary outcome in this trial will be analysed following the intention-to-treat principle as well as the per-protocol principle. The difference between the two groups will be evaluated with a 95% confidence interval (CI) using a generalised linear mixed model to express the precision of the estimate. In this model, the NRS pain score and the group will be considered the dependent variable, the imbalanced baseline characteristic will be considered the covariate, and the centre will be considered a random effect.

The secondary outcomes will be analysed with Pearson chi-square tests and expressed with 95% CIs. Each *P*-value reported in this trial will be two-sided.

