### Data Collection and Monitoring

After informed consent is obtained from the patients, the data will be collected by a research nurse who is blinded to the allocation to ensure the integrity of evaluation and prevent bias. Demographic information, including age, body mass index (BMI), PSA level, DRE results, prostate volume and American Society of Anesthesiologists (ASA) classification will be collected before anaesthesia. The pain score will be measured and recorded *via* form 1 (Figure 4) at 10 min, 1, 6, and 24 h after the biopsy. Additionally, the pain of phlebotomizing and the pain at the first moment the needle touches the skin during anaesthesia will be used as the reference and baseline for the pain assessment (form 1). During the biopsy, the external manifestations of pain will be measured *via* form 2 (Figure 5), and the blood pressure, heart rate and breathing rate will be recorded by a multi-parameter monitor. The site of needle core will be reported, because the targeted cores of the anterior zone might be associated with more pain in comparison with those of the peripheric zone (19). Before the participant is dismissed, the anaesthesia satisfaction assessment will be collected *via* form 3 (Figure 6). The pathologic data will be collected within 2 weeks after the biopsy. All of these data will be entered into a particular database. An independent monitor from the APROPOS operation group will check the quality of the data at least twice a week. The monitor may pose queries to the data, and the validity of the data will not be confirmed unless the questions have been resolved.

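### The primary model takes as covariates whichever baseline characteristics turn out imbalanced, with no criterion, and so forgoes power that covariates named in advance would give

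*Protocol article*

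**What the plan says.** The Statistical Analysis section of the protocol article promises a between-group comparison for the primary outcome: "The difference between the two groups will be evaluated with a 95% confidence interval (CI) using a generalised linear mixed model". It then assigns the roles in that model:

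- outcome, group and covariates: "the NRS pain score and the group will be considered the dependent variable, the imbalanced baseline characteristic will be considered the covariate";
- centre: "the centre will be considered a random effect".

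The article does not say which variables are candidates for adjustment or how imbalance is to be judged. Data Collection and Monitoring lists what is collected before anaesthesia: "Demographic information, including age, body mass index (BMI), PSA level, DRE results, prostate volume and American Society of Anesthesiologists (ASA) classification". It does not link any of these variables to the model.

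**The concern.** Two things in the model sentence are stated wrongly or fixed badly.

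**Covariate rule (the substantive point).** Covariates enter because they differ between the arms, not because they predict pain. With 1:1 randomisation any baseline difference is due to chance. The rule can therefore admit a variable unrelated to pain because it happens to differ, and leave out a strong predictor because it happens to be balanced. Since imbalance is undefined, the adjustment set is decided after the data are seen. The primary estimate, its interval and its P value all depend on that decision. This is a positive rule and not a detail left open, so an analysis plan that followed the article would inherit it.

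**Role of the group (a wording point).** The sentence puts the group on the outcome side. Read literally, such a model has no group coefficient and cannot give the difference promised just before.

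**Working it through.** **1. The plan's own figure.** Inputs from Sample Size: means 2.0 and 2.5 (difference 0.5), SD 1.0 in both arms, and "using a power of 90%, a two-sided α of 5%, and an allocation ratio of 1:1".

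- Normal approximation: n = 2(1.960 + 1.282)² × 1.0² / 0.5² = 84.1, rounded up to 85 per arm.
- Two-sample t-test: 85.03, rounded up to 86 per arm, as stated. Power at 86 per arm is 90.3% (t) or 90.6% (normal).
- Loss of 10%: 85/0.9 = 94.4, so 95 per arm and 190 in total, as stated. (172 × 1.1 = 189.2 also rounds up to 190.)

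The sample size reproduces. It rests on an unadjusted comparison of two means and is unaffected by this point.

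**2. How often chance alone triggers the rule.** With six candidate variables, assumed independent, the probability that at least one differs at level c is 1 − (1 − c)⁶:

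- c = 0.05: 1 − 0.95⁶ = 26%
- c = 0.10: 1 − 0.90⁶ = 47%
- c = 0.20: 1 − 0.80⁶ = 74%

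The unstated cut-off thus changes how likely any adjustment is from about one trial in four to about three in four.

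**3. What the rule does to error and power.** The documents give no R² for any covariate, so R² is an assumption and is varied. The simulation used 86 per arm, difference 0.5, SD 1, six independent normal covariates sharing the R² equally, least squares without a centre effect, and 6,000 trials per row.

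| R² | Imbalance cut-off | Type I error: rule | Type I error: all six fixed | Power: unadjusted | Power: rule | Power: all six fixed |
|---|---|---|---|---|---|---|
| 0 | 0.05 | 0.050 | 0.052 | 0.904 | 0.901 | 0.892 |
| 0 | 0.20 | 0.054 | 0.054 | 0.895 | 0.889 | 0.887 |
| 0.10 | 0.05 | 0.042 | 0.047 | 0.900 | 0.904 | 0.922 |
| 0.10 | 0.20 | 0.046 | 0.048 | 0.900 | 0.905 | 0.918 |
| 0.30 | 0.05 | 0.040 | 0.045 | 0.904 | 0.913 | 0.970 |
| 0.30 | 0.20 | 0.037 | 0.054 | 0.901 | 0.927 | 0.967 |
| 0.50 | 0.05 | 0.039 | 0.049 | 0.904 | 0.917 | 0.995 |
| 0.50 | 0.20 | 0.027 | 0.053 | 0.897 | 0.948 | 0.996 |

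The Monte Carlo standard error is about √(0.05 × 0.95/6000) = 0.003 for type I error and √(0.9 × 0.1/6000) = 0.004 for power.

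A second set-up had six candidates of which two were prognostic, with R² from 0.10 to 0.40. Power was about 90–94% under the rule and 93–99% with the two prognostic covariates fixed in advance, a gap of about 2–7 percentage points. Type I error under one rule applied once was 2.6–5.0%. Taking the best result over several cut-offs raised it to about 5.5–6.2%. Similar runs with six or eight candidates put the best-of-four figure between 5.4% and 6.6%.

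**4. Analytic check of the prespecified power.** Power ≈ Φ(0.5/√(2(1 − R²)/86) − 1.96):

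- R² 0.10: Φ(3.456 − 1.96) = 93%
- R² 0.25: Φ(3.786 − 1.96) = 97% (96.4% in the analytic ANCOVA check)
- R² 0.40: Φ(4.233 − 1.96) = 99%

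**5. Why the rule is conservative.** When a prognostic covariate is far out of balance it is adjusted for, and the large chance errors in the estimate are removed. When it is balanced it is left in the residual, so the standard error stays large. The test is then too cautious, and most of the available precision goes unused.

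**The case against.** Three stronger readings are tempting, and the documents support none of them.

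- **That no treatment effect would be estimated.** The preceding sentence promises a between-group difference, and the Introduction states a superiority aim. The group is plainly meant as a predictor. What remains is a wording error in the article's only statement of the primary model.
- **That the rule makes the trial underpowered or inflates false positives.** Power stays at about the planned 90%, because the trial was sized without adjustment. The higher power with fixed covariates was never planned and depends on an assumed R². One rule applied once is nominal to conservative. The excess of about one percentage point needs several cut-offs to be tried and the most favourable kept, and nothing in the article suggests that this is intended.
- **That the trial has no deciding analysis population.** The primary outcome is to be "analysed following the intention-to-treat principle as well as the per-protocol principle". A reader might infer that neither decides. Intention-to-treat is named first in a superiority trial, and which set decides is commonly left to an analysis plan, which is not shown here. It is not counted as a fault.

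One limit on the remedy also stands. Phlebotomy pain looks like a natural covariate, but no section says when it is recorded. Table 1 schedules NRS assessment only after the biopsy, and form 1 holds phlebotomy pain together with the post-biopsy scores. If it is recalled after the biopsy it is not a pre-treatment measure, and adjusting for it could bias the estimate.

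The objection does not rescue the covariate rule. It has no stated criterion, it selects on chance, and a better rule costs almost nothing.

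**Conclusion.** The point holds as a fault in how the primary model is fixed. The covariate set depends on the data and on an undefined judgement of imbalance, not on prognostic value. The cost is about 2–7 percentage points of power forgone against prespecified prognostic covariates, plus an avoidable opening for choice after the data are seen. It is not a shortfall against the design, and a single rule causes no inflation of type I error.

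These sizes assume a prognostic R² of 0.10 to 0.40, independent normal covariates, 86 analysed per arm, the article's difference of 0.5 and SD of 1.0, and no centre effect. If the covariates predict nothing, there is no power to gain. The objection that the set is chosen after the fact remains. The mislabelled group is a separate wording correction.

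**What to change.** Rewrite the model sentence in Statistical Analysis to state:

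- worst-pain NRS is the dependent variable;
- group is a fixed effect, and its coefficient with 95% CI is the primary result;
- centre is a random effect;
- a short list of covariates, named in advance on prognostic grounds from data collected before the block, is included regardless of balance.

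Delete the imbalance rule. The list could be, for example, age, prostate volume and a PI-RADS ≥3 lesion on the Visit 1 MRI. The lesion has some support in the article: it determines whether targeted cores are taken, and Data Collection and Monitoring notes that anterior targeted cores may hurt more. The article gives no evidence that age or prostate volume predicts pain, so the trial team should confirm the choice. Add phlebotomy pain only if it is confirmed to be recorded before the block. Naming no covariates at all would also remove the data dependence, but without the gain in power.

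The cost is wording and a few degrees of freedom. If the covariates prove irrelevant the loss is small: in the R² = 0 rows, fixing all six took power from 0.904 to 0.892 and from 0.895 to 0.887, about one percentage point, and a shorter list would cost less. Sample size and data collection do not change.

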## Outcomes

The primary outcome is the level of the worst pain experienced during the prostate biopsy procedure Pain will be measured by a numerical rating scale (NRS) ranging from 0 to 10, where 0 represents no pain and 10 represents the worst pain imaginable. Additionally, we will measure the pain experienced during the phlebotomizing procedure, with the pain experienced when the needle first touches the skin at the start of anaesthesia as the baseline or reference. Additionally, the adjusted NRS pain score (an adjusted score of 1 will be defined as the worst pain during the biopsy procedure minus the pain of phlebotomizing, and an adjusted of 2 will be defined as the worst pain during the biopsy procedure minus the pain of the needle first touching the skin at the start of anaesthesia) will be reported.

The main secondary outcomes are as follows:

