▸ Post-biopsy pain severity score, for which pain will be evaluated by the NRS at 1, 6, and 24 h after the prostate biopsy.▸ Changes in blood pressure, heart rate and breathing rate during the biopsy procedure, which will be measured and recorded by a multi-parameter monitor from 1 min prior to anaesthesia (initial value) to 1 min after the prostate biopsy. The change will be defined as the difference between the average value during the anaesthesia and biopsy procedures and the initial value. Additionally, the difference between the maximum value and the initial value will be assessed.▸ External manifestations of pain during biopsy, which will be assessed by a research nurse who will be blinded to the block arm during the biopsy procedure. The pain assessment will be divided into five parts: the degree of facial expression (0 points for no particular expression or smile; 1 point for an occasional grimace or frown, a withdrawn expression, or a disinterested expression, 2 points for frequent or constant quivering chin or a clenched jaw), the degree of activity (0 points for lying quietly or being in a normal position, 1 point for slight contractions of the hip muscles or slight movements of hip, 2 points for severe contractions of the hip or lifting the hip out of the bed), the degree of voice expression (0 points for quiet or normal communication, 1 point for an occasional moan or weeping sound, 2 points for constant moaning or sobbing and screaming), the degree of pacification (0 points for being peaceful and not requiring pacification, 1 point for being able to be comforted easily, 2 points for being difficult to comfort) and the degree of cooperation (0 points for being calm and cooperative, 1 point for language resistance, 2 points for body resistance).▸ Anaesthesia satisfaction, or patient satisfaction with overall anaesthesia, which will be measured by a questionnaire at 24 h after the biopsy. Five items will be included to evaluate satisfaction: whether the pain during the biopsy was less severe than expected (scores from 0 to 10, where 0 represents far less severe, and 10 represents far more severe than expected); whether the pain after anaesthesia was less severe than the pain during anaesthesia (scores from 0 to 10, where 0 represents far less severe and 10 represent far more severe); weather the patient is satisfied with the overall feeling of the biopsy (scores from 0 to 10, where 0 represents the highest level of satisfaction, and 10 represents the lowest level of satisfaction); whether the patient would recommend this type of biopsy to other patients (scores from 0 to 10, where 0 represents they would highly recommend, and 10 represents they would definitely not recommend it); and whether the patient would still want to choose this way if they have to undergo another biopsy (scores 0 to 10, where 0 represents very willing to choose it and 10 represents extreme reluctance).▸ The detection rate for prostate cancer, defined as the proportion of men with prostate cancer among those who undergo a prostate biopsy.▸ The detection rate for clinically significant prostate cancer, defined as the proportion of men with prostate cancer of International Society of Urological Pathology (ISUP) grade 2 or higher, according to the 2014 ISUP classification, among men who undergo a prostate biopsy.▸ Adverse events, which will be recorded 7 days after this trial. These events mainly include haematuria, vagal reflex, infection, urinary retention and other adverse events identified by the Common Terminology Criteria for Adverse Events (CTCAE).

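### Pearson chi-square is fixed for every secondary outcome, but four of the seven are ordered scores or continuous changes: the test is uninformative for the vital signs and inefficient for the scores

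*Protocol article*

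**What the plan says.** The Statistical Analysis section of the protocol article names two methods. For the primary outcome, the groups are compared "using a generalised linear mixed model to express the precision of the estimate". For everything else there is one sentence: "The secondary outcomes will be analysed with Pearson chi-square tests and expressed with 95% CIs". It is not limited to categorical outcomes, gives no categories or cut-points, and names no other test.

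The Outcomes section lists seven secondary outcomes:

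| Secondary outcome | How it is defined | Type |
|---|---|---|
| Post-biopsy pain | "pain will be evaluated by the NRS at 1, 6, and 24 h after the prostate biopsy"; the scale is a "numerical rating scale (NRS) ranging from 0 to 10" | ordered score |
| Vital signs | "The change will be defined as the difference between the average value during the anaesthesia and biopsy procedures and the initial value"; the "difference between the maximum value and the initial value will be assessed" as well | continuous change |
| External manifestations | "The pain assessment will be divided into five parts", each scored 0, 1 or 2; no sum is stated | ordered items |
| Satisfaction | "Five items will be included to evaluate satisfaction", each scored 0 to 10 | ordered score |
| Any prostate cancer | proportion of men biopsied | binary |
| Clinically significant cancer | proportion of men biopsied | binary |
| Adverse events | occurrence | categorical |

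**The concern.** The stated test fits the last three rows of that table and not the first four. The mismatch takes three forms.

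- A continuous change cannot be tested usefully by Pearson chi-square unless it is first cut into categories, and the article defines none.
- On an ordered score, chi-square asks whether the two distributions differ in any way. It does not ask whether one arm has less pain than the other, so it spends degrees of freedom on differences of no interest.
- A chi-square test on a table with many levels yields no interval for a mean or median difference, so the promised 95% CI is undefined for these four outcomes.

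At stake is the evidence meant to support the primary result. The abstract treats pain at 1, 6 and 24 h as the key secondary outcome. The Discussion relies on the external manifestations and monitor readings to broaden the assessment of pain control. A real difference in these could be missed.

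**Working it through.** **Inputs.** From the Sample Size section: means 2.0 and 2.5, SD 1.0 in both arms, two-sided 5%, power 90%, 86 men per arm. These are planning values for the primary outcome. The article gives no effect size or SD for any secondary outcome, so using them here is an assumption.

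**1. The plan's own figure.** Normal approximation: n = 2 × (1.960 + 1.282)² × 1.0² / 0.5² ≈ 84.1, so 85 per arm. The t-test calculation gives 85.03, so 86. The stated 86 reproduces, with power 90.3% for an unrounded normal outcome.

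**2. Continuous changes.** Suppose all 172 values are distinct. The table is then 2 × 172, each column holds one man, and with equal arms every expected count is 0.5.

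- Contribution of each column: (1 − 0.5)²/0.5 + (0 − 0.5)²/0.5 = 1.
- Total: 172, on 171 degrees of freedom, p = 0.46.

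No term depends on which arm has the larger values. A run with arm means 5 SD apart gave the same result: 172, 171 df, p = 0.46. With some tied readings the statistic is no longer exactly constant, but the table stays very sparse and the order of the values is still ignored.

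**3. Ordered 0-10 scores, by formula.** Take scores as a normal variable rounded to whole numbers, with 5 and above pooled.

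| Score | 0 | 1 | 2 | 3 | 4 | ≥5 |
|---|---|---|---|---|---|---|
| Mean 2.0 | 0.067 | 0.242 | 0.383 | 0.242 | 0.061 | 0.006 |
| Mean 2.5 | 0.023 | 0.136 | 0.341 | 0.341 | 0.136 | 0.023 |

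- Noncentrality = 86 × Σ(p − q)²/(p + q) = 9.38. On 5 df the chi-square power is 64%.
- For the t-test, rounding raises the SD to √(1 + 1/12) ≈ 1.041, so the standardised difference is 0.5/1.041 ≈ 0.480. Then 0.480 × √43 − 1.97 ≈ 1.18, and power is Φ(1.18) ≈ 88%.

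**4. The same by simulation** (rounded normal scores clipped to 0-10, 86 per arm; ranges are over repeated runs where there was more than one).

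| Assumption | Chi-square | t-test |
|---|---|---|
| 2.0 vs 2.5, SD 1.0 | 62-64% | 87-89% |
| 2.0 vs 2.5, SD 1.5 | 25-27% | 56-58% |
| 2.0 vs 2.75, SD 1.5 | 60% | 89% |
| 3.0 vs 4.0, SD 2.0 | 53% | 90% |

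The rank-sum test is within about 1 to 2 points of the t-test throughout. Other assumed shapes give a smaller loss:

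- low scores close to zero: 65% vs 82%, and 59% vs 78%;
- 0-2 items: 84% vs 91%, and 73% vs 82%.

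**5. Validity on the scores.** With no true difference, chi-square rejected in about 3.5% to 4.5% of runs at a nominal 5%, although roughly a quarter of the cells had expected counts below 5. The test is somewhat conservative there, not invalid.

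**The case against.** The strongest reply is that this is a condensed article and a fuller analysis plan may name suitable tests. That would answer a complaint about missing detail. It does not answer this one, because the article states a method, without restriction, that does not fit. If a fuller plan differs, the published sentence contradicts it.

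Several other objections stand, and they limit the point.

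- A reader might infer that chi-square is invalid for all four outcomes. On the ordered scores it holds its type I error, so there it is inefficient only. For the 0-2 items it is a tolerable choice with a modest loss.
- A reader might infer that cut-points would be picked after seeing the data. The article says nothing on cut-points, and an unseen plan could fix them beforehand. What can be said is that the choice would matter: under the borrowed values, splitting at 3 or more gives about 73-76% power, and at 4 or more about 49%.
- A reader might infer that testing the three pain times separately is an error. It is a legitimate approach; a joint repeated-measures model is a preference.
- The power figures borrow the primary outcome's values, and the loss varies with what is assumed.
- The primary outcome has its own model, and the sample size rests on that outcome alone.

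**Conclusion.** The sentence is wrong as written for four of the seven secondary outcomes.

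- **Vital-sign changes:** the stated test carries essentially no information unless the values are categorised, and no categories are given. This is arithmetic and needs no assumption about the size of the effect, only that the values are (nearly) all distinct.
- **Ordered scores:** the test is valid but wasteful. In the scenarios tried, the loss against a t-test runs from about 6-9 points for 0-2 items, through about 16-19 points for scores near zero, to as much as 37 points for the 0-10 scores. With the borrowed planning values it is about 25 points (62% vs 87%). All of these are illustrative, because the article gives no planning values for secondary outcomes.
- **Intervals:** the promised 95% CI has no defined estimand for these four outcomes. This needs no numerical assumption.

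The documents do not support the stronger reading that the trial's main conclusion is at risk: the primary analysis and the sample size are untouched. The sentence should be corrected before analysis, but this is not a fault of the most serious kind.

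**What to change.** Replace the one sentence on secondary outcomes with a statement by outcome type.

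- **Two detection rates and adverse-event occurrence:** Pearson chi-square, or Fisher's exact test where counts are small, with a risk difference and 95% CI.
- **Pain at 1, 6 and 24 h, satisfaction items and external-manifestation items:** a linear or mixed model like the one planned for the primary outcome, giving the difference and 95% CI; or a rank test with a location-shift estimate and 95% CI.
- **Changes in blood pressure, heart rate and breathing rate:** the same type of model with the initial value as covariate, or the rank alternative, again with a difference and 95% CI.

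If any score is to be dichotomised, the threshold should be written into the same paragraph.

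The cost is a wording change made before analysis. It needs no new data and no change to sample size or conduct.
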